#### **3.5. Outcomes:**

**Primary:** to compare between randomisation arms the rate of treatment for microbiologically-confirmed TB (per 1000 adult residents per year) during 3 months starting from the first ACF intervention.

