| Follow up duration           | 
1-3 months per cluster
 
Pre-intervention survey, 10-11 months of ACF intervention: cluster-initiation will be staggered over 9-months
                                                                                                                                                                                                                                                                                                                                                                   |                                                                                                                                                                                                                                                                                                                                                                                                                                                                                                          |
| Planned recruitment period   | June 2019-Mar 2020: pre-intervention survey and ACF Round 1                                                                                                                                                                                                                                                                                                                                                                                                                                                          |                                                                                                                                                                                                                                                                                                                                                                                                                                                                                                          |

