|                              | Objectives                                                                                                                                                                                                                                                                                                                                                                                                                                                                                                           | Outcome Measures/Endpoints                                                                                                                                                                                                                                                                                                                                                                                                                                                                               |
| 1 Primary Outcome            | 
To determine the impact of TB-ACF on population-level:
 
2.1 Rates of adult registration for microbiologically-confirmed TB
                                                                                                                                                                                                                                                                                                                                                                              | 
To compare between randomisation arms:
 
1.1 The rate of treatment (per 1000 adult residents per year) during the 3 months starting from the first ACF intervention, defined by entry into the District Health Office TB Treatment Register and laboratory records
                                                                                                                                                                                                                           |

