**Figure 1. Original study design.**

[figure not shown]

*Previously undefined abbreviations:* SOC= Standard of Care; k= thousand; mos= months

**Clusters randomised to the ACF intervention arm** will receive 1 round of brief door-to-door enquiry for chronic cough, repeated after 10 months, with staggered cluster initiation over 9 months. Health promotion messaging will be provided at the time of ACF, through leafleting and door-to-door interactions at the time of brief enquiry for chronic cough.

**All clusters (Enhanced Standard of Care):** Irrespective of randomisation, each facility in the study area will be provided with one study staff member (community/environmental health worker) responsible for facilitating identification of attendees with cough for TB investigations and basic infection control; receiving TB or HIV positive clients referred following ACF; and assisting District TB Officers to register patients being investigated for TB, with a special focus on men.

**Outcomes will be evaluated for months 1-3 from ACF initiation** using routine case-notification data for TB case-notification rates.

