#### 7.1.2. Enhanced surveillance of routinely diagnosed TB patients in Blantyre

In collaboration with Blantyre District Health Office (DHO), place of residence (GPS coordinates) and national TB programme data will be collected on all (~2,500 per year) TB

patients into an electronic database, together with a sputum specimen for TB microscopy and culture.

These Electronic TB Register records will be used to assign cluster-resident status (yes/no; cluster number and trial arm) for all registering TB patients during this trial, allowing cluster-level TB case-notification rates to be calculated.

For the purposes of this protocol, MLW will work with Blantyre DHO to adapt the current paper-based Presumptive TB Register, used to record patients being investigated for TB and the results of microbiological tests, into an Electronic Register that allows place of residence GPS coordinates to be captured, enabling investigation of cluster-level rates of TB investigations at primary care level (Appendix 4.3a&b Consent, Appendix 4.5a&b Patient Information Sheet and Appendix 4.4 CRF). MLW will also work with Chiradzulu DHO to add Chiradzulu District Hospital to the Electronic Register, since it has been identified that approximately 34% of patients who registered for TB treatment there in 2017-2019 came from the Blantyre urban area.

Qualitative in-depth interviews will be carried out with purposively selected patients being investigated for TB at primary care level because of cough, aiming to identify cues to action (Appendix 4.1a&b Consent forms, Appendix 4.6a&b participant information sheets and Appendix 4.8 topic guide).

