## 14. STATISTICS

### 14.1. Sample size justification

Sample sizes were initially calculated assuming a decline from the last National TB Prevalence Survey in 2013-14 given that there has been case-finding activity since then. However, the interim results from a **pre-intervention survey** show greater than anticipated decline (target of 14,511 participants will give precision of +/- 2.5 around an assumed true prevalence of 900 per 100,000 adults, assuming design effect of 1.5 from random household sampling. The increase to 15,500 allows for wastage from e.g. unreadable Xray/contaminated cultures).

Sample size calculations and statistical analyses will use established approaches for cluster-randomised trials.

The **primary trial outcome** has been changed from self-reported testing outcome to TB case notification.

For this, we assume an annual case-notification of adult microbiologically-confirmed TB to be in the range of 70 to 100 per 100,000 adults for the standard of care clusters, based on current data and trends.

An adult population of ~150,000 per arm followed over 12 months will then provide power to detect a 44% to 56% increase in microbiologically confirmed TB if  $k = 0.3$  to  $0.4$ .

Analysis will use standard methods appropriate for cluster-randomised trials, with adjustment for pre-intervention rates of adult microbiologically-confirmed TB.

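### If the primary outcome stays at 3 months, the implied 3-month slice per control cluster leaves about 67-75% of concurrent control-arm register events out of the primary comparison; a calendar-month model restricted to post-survey time could recover part of that precision

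*Combined protocol and SAP*

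**What the plan says.** Four places set a 3-month window: section 3.5 ("during 3 months starting from the first ACF intervention"), the primary-outcome row of the section 4 synopsis ("The rate of treatment (per 1000 adult residents per year) during the 3 months starting from the first ACF intervention"), the text under Figure 1 in section 7 ("Outcomes will be evaluated for months 1-3 from ACF initiation") and the primary-outcome statement in section 9.1. The synopsis row on follow-up reads "1-3 months per cluster" and adds that "cluster-initiation will be staggered over 9-months".

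The outcome comes from an electronic register that began in 2011 and is to continue (section 10.5.1). It assigns cluster and arm to every registering patient, "allowing cluster-level TB case-notification rates to be calculated" (section 7.1.2). SOC clusters receive no ACF visit.

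Two places use 12 months instead: the objectives table in section 9.1 and the power statement in section 14.1. The latter takes a control rate "in the range of 70 to 100 per 100,000 adults for the standard of care clusters", about 150,000 adults per arm and k of 0.3 to 0.4, and arrives at a detectable increase of 44% to 56%. Section 14.1 also plans adjustment for pre-intervention rates. Section 14.2 defers the detailed analysis plan.

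**The concern.** ACF windows open in different months across the roll-out, so SOC registrations in any of those months bear on what would have happened without ACF. If each SOC cluster contributes only one 3-month slice, most of that concurrent information does not enter the primary comparison. Expected counts are small: about 0.8-1.1 events per SOC cluster in 3 months, so the control rate is estimated with much noise. At stake is power that the trial could gain without collecting anything new.

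**Working it through.** **Inputs.** From the documents: 72 clusters randomised 1:1, so 36 per arm; about 4,400 adults per cluster (section 7), or 150,000 per arm (section 14.1), which is 150,000/36 = 4,167 per cluster; control rate 70-100 per 100,000 per year; k 0.3-0.4; 9-month stagger. Assumed, because the documents do not state them: two-sided 5% and 80% power.

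**Step 1: reproduce the stated figure.** For two arms of c = 36 clusters, power follows from z = √[(c − 1)(λ1 − λ0)²/V] − 1.96, with V = λ0/y0 + λ1/y1 + k²(λ0² + λ1²) and y the adult-years per cluster. At rate 100, k 0.3, increase 44% and 12 months in both arms:
- V = 2.40e-7 + 3.46e-7 + 2.77e-7 = 8.62e-7
- 35 × (0.00044)² = 6.78e-6, and √(6.78e-6/8.62e-7) = 2.80
- z = 0.84, so power is 80%

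Solving for 80% power gives 44% (rate 100, k 0.3) and 57% (rate 70, k 0.4). The stated range is therefore reproduced with 12 months in both arms.

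**Step 2: events outside the slice.** Expected SOC events are 150,000 × 0.0007 to 0.0010 = 105-150 in 12 months and 26-38 in 3 months. The share outside one 3-month window is 1 − 3/12 = 75% if the span is the 9-month stagger plus 3, 1 − 3/10 = 70% for June 2019 to March 2020, and 1 − 3/9 = 67% for 9 months.

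**Step 3: what extra SOC time buys on the rate-difference scale.** Same formula, with y0 and y1 set separately:

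| Months SOC / ACF | Detectable increase | Power at 44% (rate 100, k 0.3) | Power at 56% (rate 70, k 0.4) |
|---|---|---|---|
| 12 / 12 | 44-57% | 80% | 79% |
| 3 / 3 | 84-106% | 36% | 38% |
| 12 / 3 | 71-91% | 47% | 48% |
| 9 / 3 | not tabulated | 46% | 46% |

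At a rate ratio of 1.5 with 3/3 windows, control-arm Poisson noise is 33-37% of V, ACF-arm Poisson noise 49-55% and between-cluster variation 8-18%. Extra SOC time acts only on the first part, and the standard error falls by 13-15%.

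**Step 4: the log-rate-ratio scale.** Var = [(1/μ0 + k²) + (1/μ1 + k²)]/36, with 4,400 adults per cluster. At rate 70, k 0.4 and rate ratio 1.6:
- 3/3: (1/0.77 + 0.16 + 1/1.232 + 0.16)/36 = 0.0675, SE 0.260, z = 0.470/0.260 − 1.96 = −0.15, power 44%
- 12/3: μ0 = 3.08, variance 0.0405, SE 0.201, z = 0.38, power 65%

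Over the full input range this is 44-59% against 65-82%. The gain is larger on this scale because the control arm has fewer events whenever ACF works. These figures assume clean SOC data in every month.

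**Step 5: the survey.** Section 10.4.1 screens about 215 adults in every cluster of both arms and helps those who test positive to register for treatment. Sections 3.7 and 4 put survey and ACF in the same June 2019 to March 2020 period. At the initial yield in section 5.1.1 (200 per 100,000):
- 215 × 0.002 = 0.43 cases per cluster
- against 4,400 × 0.0007 to 0.0010 = 3.08-4.40 events in 12 months, this adds 10-14%
- a true ratio of 1.6 becomes about 1.6/1.14 = 1.40 to 1.6/1.10 = 1.45

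In ACF clusters the survey precedes the visit, so its cases fall mostly before months 1-3. Month terms cannot remove a difference between arms within the same month.

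**Step 6: simulation with the survey included.** Staggered starts, calendar-month terms and cluster-robust standard errors; true rate ratio 1.6. Figures carry some Monte Carlo error.

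| Analysis | Power |
|---|---|
| 3 v 3 months | 43-54% |
| ACF 3 v every SOC month, survey cases counted | 41-58% (estimate pulled to about 1.40-1.45) |
| ACF 3 v SOC months after own survey | 55-71% |
| ACF 3 v every SOC month, survey-referred cases excluded | 62-78% |

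**The case against.** Equal-length concurrent windows are a legitimate design when notifications are falling, as section 6.1 says they are, and they avoid relying on a modelled time trend. That stands against pooling a crude 12-month SOC rate with 3-month ACF rates. It does not stand against month terms, which compare ACF and SOC clusters within the same calendar month.

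The strongest objection is the survey. Not every SOC month is clean control data, and a model that used them all would be biased toward no effect and gain little or nothing (steps 5 and 6). This stands in full and is why SOC time must be restricted. The 10-14% inflation assumes that all survey cases register and that the surveys fall within the roll-out.

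The SOC window is also inferred: no section defines when it starts or says that other SOC events are unused, and the detailed plan is still to come.

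A reader might infer that most control data are thrown away and power is lost for nothing. The documents do not support that. Pre-intervention events feed the planned covariate, time trends by arm are a specific aim (section 6.2), and using the extra months has a price in assumptions. Nor does the ACF arm's own 3-month window, the larger source of noise in step 3, change.

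**Conclusion.** The point holds as a conditional gain in efficiency. If the outcome stays at 3 months and each SOC cluster contributes one 3-month slice, about 67-75% of concurrent SOC events are outside the primary comparison. Using post-survey SOC time would raise power at a rate ratio of 1.6 from about 43-54% to about 55-71% (62-78% if survey-referred cases can be excluded). On the rate-difference scale the gain is about 10 points at the protocol's own 44-56% effects. That figure takes 12 clean SOC months, so it is an upper guide for the post-survey version.

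The size rests on 36 clusters per arm, 4,400 adults (4,167 on the rate-difference scale), 70-100 per 100,000, k 0.3-0.4, two-sided 5%, evenly spread starts and a calendar trend common to both arms.

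It would be wrong to conclude that this rescues the sample-size statement. The 44-56% is reproduced only with 12 months in both arms; with SOC 12 and ACF 3 months, power at those effects is still only 47-48%. The 12-month text in sections 9.1 (objectives table) and 14.1 must be reconciled with the 3-month text in sections 3.5, 4, 7 and 9.1. If 12 months is adopted, this point largely lapses.

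**What to change.** First settle whether the primary window is 3 or 12 months, and restate power to match. If it is 3 months, pre-specify in the SAP:

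- The estimand stays the ACF effect in months 1-3 after the cluster's visit.
- Data are cluster-by-calendar-month counts. ACF clusters contribute months 1-3. SOC clusters contribute all concurrent months after their own pre-intervention survey is complete. Alternatively, SOC clusters contribute all concurrent months with survey-referred registrations excluded in both arms, if these can be identified.
- State how late survey registrations are handled, in the same way in both arms, since culture results may take up to 6 weeks (section 10.4.1).
- The model is Poisson or negative binomial, with a population offset, calendar-month terms, the planned pre-intervention rate covariate, and cluster-robust standard errors or a cluster random effect.
- The matched 3 v 3 month comparison is kept as a sensitivity analysis, with the SOC window start defined.
- The synopsis follow-up row is reworded so that its 1-3 months applies to ACF clusters only.

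The cost is SAP and synopsis wording, survey completion dates by cluster (or a flag for survey referrals), and somewhat more modelling. No new outcome data are needed. The price is reliance on a calendar trend common to both arms.

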## 5. BACKGROUND AND RATIONALE

### 5.1. Tuberculosis (TB) in high HIV prevalence settings

#### 5.1.1. Burden of TB disease

TB has been the leading cause of adult deaths from an infectious disease, globally, since 2011, with an estimated 10.0 million new TB cases and 1.6 million TB deaths, including 900 thousand cases and 300 thousand deaths in people living with HIV (PLHIV), in 2017 (1). HIV infection greatly increases the risk of progression from TB infection to TB disease, and also increases the risk of death when TB disease does occur. Because of the regional magnitude of the HIV epidemic, Southern Africa has the highest TB incidence of any global region, with an estimated 84% of all HIV-related TB deaths, globally (1,2).

Prospects for TB control in Africa have changed dramatically in the last 15 years with the highly successful scale-up of antiretroviral (ART) services and global health initiatives for funding TB and HIV programmes (2,3). However, there is still no accurate but low-cost TB test that can be reliably delivered at the point-of-care to diagnose pulmonary disease (4-5). Accessing TB diagnosis remains highly problematic, notably so for adult men who account for most TB cases and deaths but are not as well served as women by TB or HIV programmes (1,2,5-8). This maintains high prevalence of undiagnosed TB (>1% prevalence in urban Blantyre in 2013-14), and hence transmission rates, within communities. Of note, most transmission events occur to casual contacts, limiting the effectiveness of contact tracing strategies, and most TB in high transmission settings results from recently acquired TB infection (9).

Without control of ongoing TB transmission, the full potential of ART and preventive therapy for HIV-positive individuals may not be realized for decades: rapid declines in TB incidence in this region require combined prevention strategies including improved case-finding and treatment (10,11). In Malawi, for example, smear-positive TB case-notifications declined by 16% over a 12 year period when ART coverage (proportion of HIV-infected people retained on ART) increased from <0.5% to 41%, and have declined further since then (12) but are unlikely to the WHO EndTB strategy targets endorsed for 2022 and 2030 unless the large TB-testing gap can be reduced, including for men (13-15).

Recent TB prevalence surveys including 11 African countries, provide the first regionally representative data since the 1960s (16,17). These confirm the same key findings first reported from subnational surveys in South Africa and Zimbabwe (18,19). Meta-analysis of 86 surveys with 3.1 million participants shows (16): -

- much higher than anticipated rates of undiagnosed infectious TB --- the main driver of TB transmission --- prompting 2 upward revisions of WHO Global TB estimates
- men and urban residents at disproportionately high risk of undiagnosed TB
- prolonged infectiousness before diagnosis or death (median 2.6 years for men and 1.6 years for women) as deduced from comparison with case-notification data
- most survey participants with undiagnosed infectious TB being HIV-negative, even in African countries.

In Malawi and neighbouring Zambia, 2013/14 prevalence surveys report 901 and 993 culture-positive participants per 100,000 urban adults screened, respectively (16), with approximately 2.4 undiagnosed TB cases for every case diagnosed in any given year in Malawi. However, the pre-intervention prevalence survey conducted as the first phase of this study has initial

results showing only 200 confirmed TB positive participants per 100,000 urban adults screened.

### **5.1.2. Population-based active case-finding (ACF)**

At high prevalence, population-based active case-finding (ACF) for TB has potential to rapidly improve control and reduce TB transmission rates and can even be cost-saving if a sufficiently high efficiency of case-finding can be delivered at costs below a threshold proportional to the costs of treating TB (20). Recognising the importance of undiagnosed TB, but also the potential waste of resources and harms from poorly-conducted interventions, the 2013 WHO TB Systematic Screening Guidelines provide conditional support for ACF interventions in geographically defined communities with a prevalence of undiagnosed TB of 1% or more (5).

Population-based ACF was used extensively in the Northern Hemisphere until the 1970s based on radiology screening algorithms that, although highly sensitive, requires capital investment and skilled operators not readily available in low-income countries (5,21,22). Significant reductions in the prevalence of undiagnosed TB were also reported more recently from Vietnam, in a cluster-randomised trial that conducted annual collection of sputum for Xpert MTB/RIF regardless of symptoms from all adult residents for 4 successive years (23).

A less costly ACF intervention has been used in several African countries, based on encouraging participants to volunteer chronic cough to outreach or door-to-door teams for investigation with smear-microscopy for TB diagnosis. In Harare, Zimbabwe, estimated per-round efficiency was 20-25% (proportion of all undiagnosed cases found) (24), but population-level smear-positive TB case-notifications were doubled and accompanied by rapid and substantial reductions (before-to-after unadjusted -43%; adjusted -41%) in undiagnosed infectious TB from 5 rounds of ACF delivered over 2.5 years (24). Although less robust than a randomized design, this magnitude of effect within a short timeframe still meets criteria for likely causality (22).

Introducing the Harare model (ACF using 6-monthly enquiry for chronic cough, investigated using smear-microscopy) to high-density neighbourhoods in Blantyre, Malawi, during 2012-14 doubled smear-positive TB case-notification rates with a similar time-trend as seen in Harare. A similar effect has been reported from interventions using periodic direct enquiry for chronic cough with sputum collection in the community in rural Ethiopia and urban Brazil (25,26).

Mathematical modelling suggests a likely pronounced effect on underlying TB epidemiology, with a projected marked decline in undiagnosed TB prevalence (as in Zimbabwe and Vietnam) and new incident TB cases. However, ACF-interventions have not yet been accompanied by the anticipated “accelerated decline” in TB case-notification rates post-ACF intervention (17). TB case-notification data are a complex mix of disease episodes, with any given case reflecting TB transmission that could have occurred anywhere between a few weeks to many years ago.

In the absence of a prevalence survey data in Malawi, we investigated whether or not there may have been a relatively long-lasting behaviour-change --- whereby individuals who have interacted with the ACF team may have been “behaviourally primed” to act more promptly when they next develop TB symptoms. Behavioural priming is thought to have contributed to the success of a household case-finding study in Zambia and South Africa (as a larger effect was seen than could be explained by TB cases found or prevented), and also provided a better fit to a mathematical model of the Blantyre ACF data than could be obtained without

making this assumption. An initial pilot study in Blantyre has provided data to support long-lasting behaviour-change, with lasting recall of the ACF intervention and its key messages demonstrated by community-members 2 years after the last round of ACF.

